### Study sites

The two study units are a 27-bed mixed cardiac medical-surgical unit and a 22-bed cardiac stepdown unit.

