### Enrollment/randomization

Patients presenting to and discharged from participating units are enrolled automatically. As a cluster, crossover trial, randomization was limited to which unit the intervention would be deployed to first. Unit nursing staff were invited to participate in online surveys by e-mail, with reminders through staff meetings; their participation is voluntary.

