All unit staff will be exposed to the intervention throughout the study, although after the first month of the study only those staff on the unit initially randomized to the intervention will have been exposed. This provides an opportunity for a comparison between exposed and unexposed staff. We note that patients present on the unit during the time of crossover are exposed to both the intervention and the control conditions. To avoid crossover effects and eliminate the logistical challenges of changing any behavioral care provider team during the admission, patients are excluded if they are present on a unit during crossover. This does lead to some possibility of contamination, since the BIT may be present in a unit during a control condition. However, the BIT comprises just two providers who were given strict instructions to avoid such contamination and who were also provided with training on how to defer questions or requests that would have resulted in contamination.

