Anonymous surveys will be used to measure staff perceptions of their ability to manage disruptive patient behavior as well as their experience with the BIT. The behavioral health survey previously used at the organization is a 10-item instrument that assesses staff perceptions of workplace violence and safety (Table 1). The 10-item scale was adapted from prior work by Loucks et al. [9] and Rutledge et al. [12], who have validated the Behavioral Health Care Competency Survey. The survey was evaluated for content validity for the current purpose. For this study, we have adapted these instruments to be administered to nursing staff on the two participating units at three different time points: prior to the study, following the first 1-month intervention period, and after the study period has been completed (see Fig. 1). The surveys will be conducted electronically using Research Electronic Data Capture (REDCap) [5]. REDCap allows for surveys completed by the same individuals to be linked while maintaining the anonymity of respondents by preventing access to the linkage tables held securely within the REDCap application.

**Table 1 Tab1:** Behavioral health survey to assess staff perceptions of workplace violence and safety

1. Have you encountered patients exhibiting disruptive, threatening, or acting out behavior?					
Yes					
No					
2. If yes, did their behavior in any way impact your ability to provide care?					
Yes					
No					
3. Please specify how care was impacted (select all that apply):					
Patient was non-compliant with care					
Took time away from care with other patients					
Disruptive to unit and other patients					
Patient was combative					
Other (please describe)					
4. In your current position, which of the following did you experience while caring for a patient exhibiting disruptive, threatening, or acting out behavior? (Select all that apply.)					
Physical (hit, kick, slapped, shoved, spit at, thrown objects, grabbed, bitten, or attacked)					
Verbal (threatening, bullying, harassing, name calling, blaming, insulting, yelling, cursing, intimidation)					
Elopement					
Central line manipulation related to substance abuse					
Suicidal ideation					
Self-injury					
Other (please describe)					
5. Did you experience any of the following because of caring for a patient exhibiting disruptive, threatening, or acting out behavior?					
	Never	Rarely	Sometimes	Often	Always
Fear for personal safety					
Fear for patient safety					

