### Primary outcomes

This study has two primary outcomes: (1) any documented interventions to manage disruptive, threatening, or acting out behavior, and (2) staff self-reported comfort with and ability to manage patients exhibiting disruptive, threatening, or acting out behavior. Documented evidence of intervention is defined as:
Violence controlInjurious behaviorAdministration, including as-needed administration, of the following medications for behavior management: quetiapine (Seroquel), alprazolam (Xanax), clonazepam (Klonopin), haloperidol (Haldol), lorazepam (Ativan), olanzapine (Zyprexa), risperidone (Risperdal), and ziprasidone (Geodon).

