***Primary***		
**Violence control measures utilized, or patient injurious behaviors reported**	Composite of violence control nursing intervention; PRN medication administration of quetiapine, alprazolam, clonazepam, haloperidol, lorazepam, olanzapine, risperidone, or ziprasidone for behavior management; or nursing problem of violence risk or injurious behavior	Extraction of nursing documentation and medication administration from the electronic health record
**Nurse comfort and confidence in their ability to manage patients exhibiting disruptive, threatening, or acting out behavior**	Staff perceptions of workplace violence/safety, as well as perceived confidence, comfort, and most helpful training/support received	A behavioral health survey administered via Research Electronic Data Capture (REDCap) prior to intervention, 1 month after intervention began, and at the conclusion of the intervention

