### Statistical analysis principles

There are two main analyses. The first will compare outcomes between patients exposed to the BIT and patients not exposed to the BIT. The outcomes are quantitative variables that are either binary or ordinal in nature. Comparisons will use logistic regression or proportional odds models, adjusted for covariates. The models will include cluster (unit) as a random effect and will also include period, including the following patient characteristics: age, sex, race, comorbidities, reason for admission, and psychiatric diagnoses.

The second analysis will compare staff perceptions between those exposed to the behavioral intervention and those not exposed to the behavioral intervention during the first month, and will also compare perceptions before exposure to the behavioral intervention with perceptions after the study concludes. We will compare categorical variables using chi-square tests, and we will compare continuous variables using paired or independent samples *t* tests as appropriate. For continuous data that are non-normally distributed, and for ordinal variables, we will use the Mann-Whitney *U* test or the Wilcoxon test as appropriate.

While our initial approach is a simple comparison, this ignores the repeated measurements. Since staff on the unit can leave and new staff can join the unit, we will use a mixed-effects model to analyze differences between before the study, at 1 month after the intervention began, and on completion of the study. Respondents will be included as a random effect. Linear, logistic, or proportional odds models will be used as appropriate for the outcome. Finally, we may model the survey outcomes using similar regression techniques to explore factors associated with changes in staff perceptions.

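### The month-1 staff comparison sets one unit against the other with unadjusted tests, and the mixed model as described contrasts survey times only, so neither separates the BIT effect from a unit difference or a trend

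*Protocol article*

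**What the plan says.** The article's Primary outcomes section names as its second primary outcome "staff self-reported comfort with and ability to manage patients exhibiting disruptive, threatening, or acting out behavior"; Table 2 words it as comfort and confidence. In the survey (Table 1), item 6 measures comfort on five ordered levels and item 10 measures confidence from 0 to 10.

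The design has two clusters, "a 27-bed mixed cardiac medical-surgical unit and a 22-bed cardiac stepdown unit" (Study sites). Under Enrollment/randomization, "randomization was limited to which unit the intervention would be deployed to first". The Intervention section draws the consequence for staff: "after the first month of the study only those staff on the unit initially randomized to the intervention will have been exposed". By the end of the study all staff have been exposed.

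Statistical analysis principles then set out three staff analyses:

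- At month 1, to "compare staff perceptions between those exposed to the behavioral intervention and those not exposed to the behavioral intervention during the first month".
- A comparison of perceptions before exposure with perceptions after the study ends. For this and the month-1 comparison the tests are chi-square, paired or independent t, Mann-Whitney or Wilcoxon.
- Because the simple comparison ignores repeated measurements and staff come and go, "we will use a mixed-effects model to analyze differences between before the study, at 1 month after the intervention began, and on completion". Respondent is the random effect.

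The patient model in the same section names unit and period. The staff model names neither. A pre-study survey is taken on both units, and under Data collection "REDCap allows for surveys completed by the same individuals to be linked".

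**The concern.** At the month-1 survey every exposed respondent works on one unit and every unexposed respondent on the other. The units differ in size and type, so their staff may differ in comfort and confidence before the BIT arrives. An unadjusted test between them cannot tell that difference from a BIT effect. Randomizing which unit goes first decides the sign of the difference by chance. With one unit per condition, though, the difference does not enter the standard error of a test that treats respondents as independent.

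The mixed model is introduced to deal with repeated measurement and turnover, not with this confounding, and the contrast it states is between survey times. At stake is a significant result on a primary outcome that reflects a pre-existing unit gap or a trend common to both units.

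**Working it through.** The article gives no sample size, effect size or power for the staff outcome, so there is no stated figure to reproduce. The check has four steps.

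**1. What each contrast estimates.** Let g be a stable gap between the first-deployed unit and the other, s a change common to both units, and d the BIT effect. Take equal numbers per unit, and the same s and d at month 1 and at the end.

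| | Baseline | Month 1 |
|---|---|---|
| First-deployed unit | g | g + s + d |
| Other unit | 0 | s |

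- Month-1 exposed minus unexposed: (g + s + d) − s = g + d.
- Month 1 minus baseline, units pooled: [(g + s + d) + s − g − 0]/2 = s + d/2.
- End minus baseline, all staff exposed: s + d.
- Change on the exposed unit minus change on the unexposed unit: (s + d) − s = d.

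In SD units, with d = 0 and g = 0.25, the month-1 comparison shows 0.25. With d = 0 and s = 0.25, both time contrasts show 0.25. With d = 0.5 and s = 0, the pooled month-1 time contrast shows only 0.25.

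**2. False-positive rate of the month-1 test.** Assumed, not in the article: n = 25 to 60 respondents per unit and a unit-level ICC of 0.02 to 0.05. The design effect is DE = 1 + (n − 1) × ICC. The rejection rate with no BIT effect is 2 × [1 − Φ(1.96/√DE)].

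| n per unit | ICC | DE | 1.96/√DE | Rejection rate |
|---|---|---|---|---|
| 25 | 0.02 | 1.48 | 1.61 | 10.7% |
| 40 | 0.02 | 1.78 | 1.47 | 14.2% |
| 40 | 0.05 | 2.95 | 1.14 | 25.4% |
| 60 | 0.05 | 3.95 | 0.99 | 32.4% |

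A variant that puts the within-unit variance into the naive standard error gives 12.3% and 22.2% at n = 30, and 16.8% and 30.4% at n = 50, for the same two ICCs. Simulation agrees within about one percentage point.

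With a fixed gap and no BIT effect, the probability of a significant result at 20 to 50 per unit is 0.12 to 0.24 for a 0.25 SD gap and 0.35 to 0.71 for a 0.5 SD gap.

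**3. The unit-by-time contrast under the same kind of assumptions.** With 30 per unit and a within-person correlation of 0.6, simulated type I error is 0.050 to 0.052 when the unit effect is fully stable (ICC 0.02 to 0.10). If 10% to 20% of the unit variance changes between surveys, it is 0.07 to 0.09 at ICC 0.02, 0.10 to 0.14 at ICC 0.05, and 0.15 to 0.22 at ICC 0.10.

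**4. Precision.** With complete pairs, equal variances and baseline/month-1 correlation r, a change has variance 2(1 − r) times that of a single month-1 score. The relative variance is 1.00 at r = 0.5, 0.80 at r = 0.6, and 1.20 at r = 0.4.

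**The case against.** Four points can be made for the plan.

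- **Silence is not exclusion.** The article is condensed. It names a contrast and a random effect for the staff model but gives no complete list of fixed effects. A reader might infer that the plan rules out a unit or exposure term; the text does not say so. It remains true that the article fixes the comparison, the tests and the model's contrast for a primary outcome, and names unit and period for patients only. The further modelling of survey outcomes is optional and exploratory.
- **Part of the limit is acknowledged.** The Discussion concedes that spillover and a secular trend cannot be conclusively separated. This covers much of the pre/post problem. It does not mention that exposure coincides with unit in the month-1 staff comparison. Presentation of the results commits to comparing all three surveys, but not by unit.
- **The limit lies in the design.** There is one unit per condition whatever model is used. A reader might infer that the unit-by-time contrast isolates the BIT effect. It does so only if the unit gap is stable and the trend is common, as step 3 shows. This stands, and the fix has to say so.
- **The rejection rates rest on assumptions.** A reader might take 11% to 32% as this trial's error rate. The article gives neither respondent numbers nor an ICC, so the figures show direction only.

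Two further inferences are not supported. Using the baseline does not guarantee a gain in precision: the change contrast gains only when r exceeds 0.5, and pairs will be incomplete because participation is voluntary and staff turn over. Nor is there a basis for ranking confidence above comfort, since the primary outcome names comfort in both the text and Table 2.

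**Conclusion.** The point holds. At month 1 staff exposure and unit are one variable, the planned tests are unadjusted, and they estimate g + d. The mixed model, on the terms stated, estimates s + d/2 at month 1 and s + d at the end. None of these equals d unless the unit gap or the common trend is zero and, for the pooled month-1 contrast, not even then. This follows from the article's own design and needs no assumed numbers.

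The size does need them: about 11% to 32% false rejection for 25 to 60 respondents per unit and a unit ICC of 0.02 to 0.05. A linkable baseline survey on both units allows a contrast that removes a stable unit gap and a common trend. It cannot remove change specific to one unit, so a confirmatory claim for this outcome is out of reach under any analysis of these data.

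**What to change.** - Add unit and unit-by-time terms to the planned respondent mixed model. Make the baseline-to-month-1 unit-by-time contrast (change on the exposed unit minus change on the unexposed unit) the main staff analysis for both comfort (item 6) and confidence (item 10).
- Report the cross-sectional month-1 tests and the pre/post change as descriptive.
- State that with one unit per condition the interval omits unit-specific change over time, so the result is not confirmatory.
- Date the change. Trial status puts the end of enrollment at 30 December 2019 and the last surveys in January to February 2020, so the change should be recorded as made after data collection.

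The cost is analysis wording and two model terms; no new data are needed. The price is a more modest claim for this primary outcome, and no gain in precision over the cross-sectional test unless the baseline/month-1 correlation exceeds 0.5.

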### Treatment of outliers

Our evaluation of whether or not an individual patient experiences an event reduces the impact of outliers on the primary outcome. For survey results, the results are constrained to the available options, again limiting outliers. Therefore, any statistical modeling will not evaluate the impact of outliers. There is the possibility that there are outliers for variables such as length of stay or for counts of behavioral problems. These are expected and will be reported. These outcomes will generally be compared between groups or modeled using non-parametric approaches, which are robust to the presence of such outliers.

### Presentation of the results

After completion of enrollment and data analysis, the results of the trial will be communicated to the public through manuscript publication and submission of the results to the ClinicalTrials.gov database. Submission for publication will include public access to the full study protocol and statistical code. Authorship will be based on the International Committee of Medical Journal Editors guidelines [6], and professional writers will not be used.

The flow of patients through the study will be presented in a flow diagram (Fig. 1). Baseline characteristics will be presented by treatment group, as shown in Table 2. The percent of patient injurious behaviors reported will be determined by extracting reports of biting, kicking, throwing, etc., from the EHR. The percentage of violence control measures used will be determined by extracting medications, restraints, and sitters ordered from the EHR.

A composite of all documented indications of disruptive patient behavior, including violence control nursing interventions, as-needed (PRN [*pro re nata*]) medication administration for behavior management, nursing problem of violence risk, or any injurious behavior, will be extracted from the EHR. Each component of the primary outcome will also be reported separately, along with documented physical restraints for disruptive patient behavior.

The percentage change in nurse comfort and confidence in their ability to manage patients exhibiting disruptive, threatening, or acting out behavior; in perceptions of workplace violence/safety; and in perceived confidence, comfort, and most helpful training/support received will be determined by comparing surveys conducted pre-implementation, 1 month after the intervention began, and post-implementation.

The rate of unit nursing staff retention will be determined by extracting rates from internal human resources records. Patient length of stay will be determined by extracting data from the EHR.

## Discussion

Upon completion, the DEMEANOR study will provide the most comprehensive data to date on the impact of a proactive behavioral intervention on disruptive, threatening, or acting out events in adult hospitalized patients.

Several potential threats to the validity of the trial exist. As the primary and secondary variables are being collected from documentation in the EHR, the potential for incomplete data exists. Additional limitations in using EHR data in clinical research include ensuring data security and privacy and overcoming challenges associated with linking clinical data from diverse systems [3]. The use of sitters or virtual sitters and restraints is dependent on a variety of patient care conditions, and verifying those that pertain to disruptive patient behavior will be dependent on clinical documentation or specific ordering directives.

There is a possibility that patients hospitalized during the study period who did not receive a specific consult from the behavioral intervention team (BIT) nonetheless benefited from the presence of the team. The study design does not allow a conclusive differentiation between a spillover effect on the units where the BIT is implemented and a possible secular trend from other unmeasured influences on the primary or secondary outcomes. Consults on the control unit during the study period will be monitored to assess for the potential for an increase due to staff awareness and exposure to the BIT during the crossover periods. Potential fluctuations in patient census during the trial and also the number of patients presenting with behavioral comorbidities or those exhibiting disruptive behavior may also impact the study results.

Nursing response rates to the pre-study, 1 month, and post-implementation surveys may impact the ability to evaluate change in perceptions of their ability to manage patients exhibiting disruptive, threatening, or acting out behavior. Also, nursing retention rates are dependent on a number of factors, including career opportunities which may not be related to nursing job dissatisfaction or to encountering patients with disruptive behavior.

The DEMEANOR study is a pragmatic trial which provides the opportunity to evaluate the effectiveness of an intervention in real-life routine practice conditions [10]. It also allows us to consider the infrastructure and costs associated with implementing this type of program so that the results can be placed in this context. Inherent in this design however is the potential for a lack of external validity. Additionally, with a single-center trial, there is limited ability to generalize the study results.

## Trial status

The DEMEANOR study is an ongoing, single-center, pragmatic, crossover trial that will provide comprehensive information on the impact of a proactive behavioral intervention on disruptive, threatening, or acting out events in adult patients. The protocol is the current version (number one). Patient enrollment began on 1 March 2019, and enrollment ended 30 December 2019. Post implementation nurse surveys were completed between January and February 2020.

## Data Availability

On completion of the study, investigators external to the research team may request to collaborate on secondary analyses. With appropriate IRB approval and data use agreements in place, de-identified datasets may be released. All statistical code will be made publicly available with the analysis. The investigators plan to publish trial results without assistance from outside professional writers. The investigators have no publication restrictions.
